### Statistical methods

#### Sample size calculation

Sample size estimates were based on a cluster-randomized design and calculated using the *clustersampsi* command (Stata version 15.0). Drawing on pilot data (mean SI!-Child score excluding nicotine exposure at ages 7-8 = 70.62; SD = 11.77), a minimum of 40 schools (20 per study arm) was required to detect a 5% difference in SI!-Child score (excluding nicotine exposure) between groups, with 80% power and a 2-sided significance level of 0.05.

Additional parameters included an average of 20 children per school, a coefficient of variation of cluster (school) sizes of 0.51, and an intraclass correlation coefficient of 0.05. To account for potential loss to follow-up, the target sample was increased to 42 schools (21 per arm), corresponding to an expected enrollment of 840 children.

#### Statistical analysis plan

The descriptive analysis will summarize baseline data, including demographic variables (eg, gender, age, place of birth), socioeconomic indicators (eg, household income, parental or caregiver education level and country of birth), and study-specific variables (eg, SI!-Child scores; lifestyle habits such as diet, sleep, and PA; adiposity measures; and blood parameters). Continuous variables will be presented as means and SDs, and categorical variables as frequencies and percentages.

Primary endpoint differences will be evaluated using all available measurements at baseline and at 5-year follow-up. The intervention effect will be estimated using multilevel mixed-effects models for repeated measures. The model will include fixed effects for time of assessment (baseline vs follow-up), randomization group (reintervention vs single-intervention), and the interaction between time and randomization group. The treatment effect will be estimated from the time-by-randomization interaction term, representing the between-group difference in change in SI!-Child score over time. Random intercepts for school and participant will be included to account for clustering at the school level and repeated measurements within individuals. Similar multilevel mixed-effects logistic regression models will be applied for categorical outcomes, and the same analytical strategy will be used to evaluate secondary endpoints.

The primary analysis will follow the intention-to-treat principle, including all randomized enrolled participants according to their allocated group. Models will be estimated using maximum likelihood, which provides valid inference under a missing-at-random assumption and uses all available data without requiring imputation. Models may additionally adjust for prespecified baseline covariates (eg, baseline outcome value, age, gender, and stratification variable) to improve precision.

Sensitivity analyses will be conducted to evaluate the robustness of the findings to alternative assumptions about missing data. These will include 1) complete-case analyses restricted to participants with both baseline and follow-up outcome measurements; 2) multiple imputation procedures; 3) additional sensitivity analyses exploring potential missing-not-at-random mechanisms, and other statistical approaches such as cluster-level analyses or Analysis of Covariance models of follow-up outcomes adjusted for baseline values.

The SI! Program Reintervention design permits the simultaneous testing of multiple hypotheses. For each research objective, a specific statistical analysis plan will be developed. At each assessment time point, cross-sectional associations between independent variables and outcomes of interest will be evaluated using multivariate linear regression models for continuous variables and logistic regression models for categorical variables. Covariate adjustment will be defined a priori based on the specific research question and determined through a combination of clinical relevance and statistical criteria.

All statistical analyses will be conducted using Stata 15.0 or higher (StataCorp) or R software.

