### Data collection

The schedule of enrollment, interventions, and assessments for the SI! Program Reintervention trial is summarized in Figure 3. Full participant assessments are scheduled at baseline and at 3- and 5-year follow-up. These include the complete set of LE-8 components, with detailed evaluation both of health behaviors (diet, PA, nicotine exposure, and sleep health) and of health factors (body mass index [BMI], lipid profile, blood glucose, and blood pressure [BP]), as well as body composition indicators such as waist circumference (WC) and body fat mass.

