**Figure 3 fig3:**
[figure not shown]
**Study Timeline of the SI! Program Reintervention Trial** Timeline of enrollment, intervention delivery, and assessment activities for schools enrolled in phase I and phase II of the SI! Program Reintervention trial. The figure shows the planned time points for classroom intervention, environment reinforcement (school and home), full health assessments, short survey, and implementation checklists, spanning academic years 2023 to 2031.

Measurements will be conducted during school hours by a team of trained nutritionists and nurses. Parents/caregivers will complete questionnaires about their child’s and their own lifestyle behaviors through a dedicated data management application, due to the limited ability of young children to accurately report these behaviors. For families without email access, printed copies will be provided.

After each assessment, families will receive a brief medical report summarizing results and including recommendations for follow-up with their primary care physician, if needed. In addition to the main assessments, families will complete short questionnaires at 1-, 2-, 4-, and 6-year follow-up (Figure 1), covering child diet, PA, nicotine exposure, sleep health, and parent/caregiver-reported weight and height. Every effort will be made to follow-up all participants, including those who change schools.

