### Definition of health scores

#### SI!-Child score

The SI!-Child score is a simplified tool adapted from the LE-8 scale to assess and monitor lifestyle-related metrics for CVH screening in children and adolescents. This score was designed to capture behavior change and facilitate repeated monitoring in educational school-based interventions. Details of its development and assessments of agreement with the lifestyle-related LE-8 components are provided in the Supplemental Methods and Results. The SI!-Child score incorporates 5 behavioral metrics derived from the LE-8 score: diet, PA, nicotine exposure, sleep health, and BMI. Each metric is scored on a 0 to 100 scale. The overall SI!-Child score is calculated as the unweighted average of the 5 components and categorized as poor (0-49 points), intermediate (50-79 points), or ideal (80-100 points)^13^ (Figure 4). In this trial, nicotine exposure will not be included in the calculation of the SI!-Child score, given the negligible prevalence of active smoking in young children and because nicotine exposure is primarily determined by environmental factors rather than direct child behavior. Therefore, the SI!-Child score will be derived as the unweighted average of the 4 remaining components and categorized according to the established thresholds.

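### The primary model leaves out the full 3-year assessment, so 5-year missingness must be random given arm and baseline information alone

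*Protocol article*

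**What the plan says.** Under Statistical analysis plan, the article restricts the primary comparison to two visits ("Primary endpoint differences will be evaluated using all available measurements at baseline and at 5-year follow-up") and codes time accordingly: "fixed effects for time of assessment (baseline vs follow-up)". Random intercepts for school and participant are the only covariance terms. Estimation is by maximum likelihood, which the article says "provides valid inference under a missing-at-random assumption and uses all available data without requiring imputation". The model may also adjust for baseline covariates. The sensitivity analyses are complete-case analysis, "2) multiple imputation procedures", missing-not-at-random explorations, cluster-level analysis and analysis of covariance on the follow-up score. None is said to use 3-year data.

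Under Data collection, the schedule is wider: "Full participant assessments are scheduled at baseline and at 3- and 5-year follow-up". Between these, "families will complete short questionnaires at 1-, 2-, 4-, and 6-year follow-up", with parent-reported weight and height.

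**The concern.** Children are enrolled in first grade at a mean age of 6.2 years and the primary endpoint falls five years later. A child seen at years 0 and 3 and lost before year 5 enters the primary model with the age-6 score only. If the chance of being lost depends on how the child was doing at year 3, a two-visit likelihood cannot account for it, although the information was collected.

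The arms also differ in exposure before year 3. The reintervention arm receives the program from second grade and the single-intervention arm only from fifth, while the 3-year visit falls in fourth grade by the grade schedule. It is therefore plausible, though not shown, that the link between the 3-year score and later dropout differs by arm. That is the case in which the effect estimate is distorted rather than merely less precise.

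**Working it through.** **1. The plan's own figure.** Inputs from Sample size calculation: mean 70.62, SD 11.77, 5% difference, 80% power, two-sided 0.05, 20 children per school, coefficient of variation 0.51, intraclass correlation 0.05.

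- Difference: 0.05 × 70.62 = 3.53 points.
- Unclustered size: 2 × (1.96 + 0.84)² × 11.77² / 3.53², which rounds up to 175 per arm.
- Design effect: 1 + ((1 + 0.51²) × 20 − 1) × 0.05 = 2.21.
- Schools per arm: 175 × 2.21 / 20 = 19.34, rounded up to 20, or 40 in total.

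The stated 40 schools is reproduced. It does not involve the 3-year visit, so the sample size is unaffected.

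**2. What each model must assume.** Write Y0, Y3 and Y5 for the scores.

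- Two visits: given arm and Y0 (and any baseline covariates), missingness of Y5 must not depend on Y3 or Y5.
- Three visits: given arm, Y0 and Y3, missingness of Y5 must not depend on Y5. Dependence on Y3 is allowed.

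**3. Bias.** The article gives neither within-child correlations nor an expected loss rate, so these are assumptions. Large-sample simulation: SD 11.77, true 5-year effect 3.53, everyone seen at year 3, and 5-year loss 20% at the average 3-year score. The log-odds of loss rise by 0, 0.5 or 1 per SD lower 3-year score. Correlations (0–3, 0–5, 3–5 years) are either all 0.5, or 0.5, 0.3 and 0.6. The 3-year effect is 0 or 3.53. Overall loss came to 19–24% per arm.

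| Dropout depends on the 3-year score | Two-visit estimate | Three-visit estimate |
|---|---|---|
| In neither arm | 3.47–3.54 | 3.47–3.54 |
| Equally in both arms | 3.30–3.58 | 3.46–3.62 |
| In the reintervention arm only | 3.74–4.69 | 3.48–3.57 |

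The first row shows simulation noise of up to about 0.06. With equal dependence the two-visit bias is about 0 to 0.2 points (3.53 − 3.30 = 0.23 at most). With one-arm dependence it runs from 3.74 − 3.53 = 0.21 to 4.69 − 3.53 = 1.16 points, or 6% to 33% of the target. The sign reverses if the dependence is in the other arm.

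**4. Precision.** Generalised least-squares variance of the 5-year group-by-time contrast with and without year 3: 25 schools per arm, 20 children each, intraclass correlation 0.05, within-child correlations 0.3 to 0.7.

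| 5-year loss | Variance reduction from adding year 3 |
|---|---|
| 0% | 0% |
| 5% | 0.1–0.9% |
| 10% | 0.3–1.9% |
| 20% | 0.6–3.9% |
| 30% | 0.9–6.1% |

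For example, with all correlations 0.5 and 20% loss, the standard error falls from 0.810 to 0.804.

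**The case against.** A baseline-to-5-year model matches the stated endpoint and is valid under its own assumption. Bias above about 0.2 points needs dropout that depends on the 3-year score differently by arm, and the article gives no evidence of this. Children lost before year 3 gain nothing from the change. The sample-size allowance for loss, from 40 to 42 schools (2/42 = 4.8%), implies less loss than the 20% assumed here. Imputation and missing-not-at-random analyses are already planned. All of this stands and limits the point to robustness. It does not remove the point, because the two-visit restriction is a stated model choice and the sensitivity analyses do not say that they use year 3.

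Three stronger readings are tempting, and the article supports none of them.

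- A reader might see a contradiction in the claim to use all available data. The opening sentence has already limited the data to two visits. Within that set the claim is fair: children with only one of the two visits are kept.
- A reader might infer that a 5-year score with one missing component is discarded. The article says only that "the SI!-Child score will be derived as the unweighted average of the 4 remaining components". It gives no rule for incomplete scores, and such a rule is commonly left to the analysis plan. Activity and sleep also share one wrist device and both have questionnaire input, so the four components should not be treated as independently missing.
- A reader might conclude that a 3-year contrast ought to be an endpoint. The stated question is the 5-year comparison. The article promises a specific analysis plan for each research objective, so adding that endpoint would be a preference.

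**Conclusion.** The point holds as a robustness weakness in the primary model. Leaving out year 3 makes the missing-at-random assumption stronger than the collected data require. At an assumed loss of about 20%, the consequence ranges from negligible to about 1.2 points against a 3.53-point target. Only arm-specific dependence takes it above about 0.2. At loss nearer the sample-size allowance, it would be smaller. Loss of precision is not a strong argument: it is nil with complete 5-year data and at most about 6% of variance at 30% loss under the assumed correlations. The loss rates, correlations and dropout slopes are assumptions throughout. The sample size is not in question.

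**What to change.** Fit the baseline, 3-year and 5-year scores jointly, with time as a three-level factor and its interaction with arm. Keep the 5-year group contrast as the primary estimate, so the estimand does not change. Replace the random-intercepts-only structure with an unstructured child-level covariance and a school-by-time random effect. With three visits, random intercepts alone force equal correlation between every pair of visits and a school effect that is constant over time, so the 3-year score could receive the wrong weight.

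At minimum, keep the two-visit model and name the 3-year score and its components as auxiliary variables in the planned multiple imputation.

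The cost is a change of wording and a few more covariance parameters to estimate. No new data are needed. The follow-up timeline runs to 2031, so the change can be fixed before 5-year outcomes are analysed.

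### The primary effect is an unconstrained difference in change; making baseline-adjusted ANCOVA primary would gain precision, by an amount that depends on a correlation the article does not give

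*Protocol article*

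**What the plan says.** In the Statistical analysis plan section, the primary model has fixed effects for time, randomization group and their interaction, with random intercepts for school and child. On the estimator it says: "The treatment effect will be estimated from the time-by-randomization interaction term, representing the between-group difference in change in SI!-Child score over time". A later sentence permits, without requiring, adjustment for baseline covariates, and names the baseline value of the outcome as one of them. Among the sensitivity analyses it lists "Analysis of Covariance models of follow-up outcomes adjusted for baseline values".

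The Sample size calculation section works from pilot data at one age ("mean SI!-Child score excluding nicotine exposure at ages 7-8 = 70.62; SD = 11.77") and is set "to detect a 5% difference in SI!-Child score (excluding nicotine exposure) between groups", "with 80% power and a 2-sided significance level of 0.05". Under these inputs, "a minimum of 40 schools (20 per study arm) was required". No correlation between baseline and 5 years is given, at child or school level.

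The endpoint is worded as a change in the Abstract and as a between-group difference at 5 years under Hypothesis and endpoints.

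**The concern.** In a randomized comparison, a model with a free group effect at baseline subtracts the whole observed baseline difference between arms, chance imbalance included. ANCOVA subtracts only the part that baseline predicts. With comparable arms and equal variance at the two times, ANCOVA is therefore at least as precise (in large samples), and strictly more so unless R = 1.

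The sample size is a follow-up-only calculation. A change score is noisier than the follow-up score alone when R is below 0.5, so the planned estimator could then deliver less than the calculation promises. ANCOVA could not, apart from a small cost in degrees of freedom. Precision on the primary question is at stake, although baseline was assessed in 963 enrolled children.

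**Working it through.** **Inputs from the Sample size calculation section.** SD 11.77 and mean 70.62; difference read as 5% of the mean, 0.05 × 70.62 = 3.531 points; "an average of 20 children per school, a coefficient of variation of cluster (school) sizes of 0.51, and an intraclass correlation coefficient of 0.05". From the flowchart caption: 26 and 24 schools, 588 and 389 children. **Assumed, because not given:** R, or equivalently the child-level correlation r and the autocorrelation c of school effects (c = 1 means constant over time); equal SD at both times.

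**1. Reproduce the plan.** Design effect = 1 + [(1 + 0.51²) × 20 − 1] × 0.05 = 2.210. An unclustered two-sample comparison needs 175 children per arm. 175 × 2.210 / 20 = 19.34, rounded up to 20 schools per arm. The stated 40 schools are reproduced, with 81.4% power (normal approximation), as a single-time comparison.

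**2. Variances.** Let V be the variance of the follow-up-only contrast.
- Planned interaction: 2(1−R)V
- ANCOVA: (1−R²)V
- Ratio, ANCOVA to planned: (1+R)/2, so the reduction is (1−R)/2

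**3. Power for 3.531 points** (normal approximation, no loss to follow-up; the recruited columns use all 977 children):

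| R | Reduction | 40 schools: planned / ANCOVA | Recruited: planned / ANCOVA |
|---|---|---|---|
| 0.3 | 35% | 67.4% / 84.9% | 75.7% / 90.9% |
| 0.4 | 30% | 74.1% / 87.6% | 81.9% / 92.9% |
| 0.5 | 25% | 81.4% / 90.9% | 88.2% / 95.3% |
| 0.6 | 20% | 89.1% / 94.6% | 94.0% / 97.6% |
| 0.7 | 15% | 95.8% / 97.9% | 98.2% / 99.3% |

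The planned estimator reaches 80% at R = 0.48 (20 schools per arm), 0.46 (21 per arm), 0.37 (as recruited), or 0.43 (as recruited with an assumed 20% fewer children per school). A noncentral t reference gives slightly lower power: at R = 0.46 with 40 schools, 76% planned against 88% ANCOVA.

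**4. What the stated random effects imply for R.** Per school, in units of SD², the between-school part is 0.05 × (1 + 0.51²) = 0.0630 and the within-school part is 0.95/20 = 0.0475, total 0.1105. So R = (0.0630c + 0.0475r)/0.1105.
- c = 1, r = 0: R = 0.57, reduction (1 − 0.57)/2 ≈ 22%
- c = 1, r = 0.5: R = 0.0868/0.1105 = 0.785, reduction ≈ 11%
- c = 0.5, r = 0.3: R = 0.0458/0.1105 = 0.41, reduction ≈ 29%

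With c = 1, R cannot fall below 0.57 for any non-negative r, so no shortfall arises. A generalized least squares check with unequal school sizes agrees. At 20 × 20 with c = 1, the reduction is 16.2%, 11.5% and 6.9% at r = 0.3, 0.5 and 0.7, and planned power is about 87% even at r near 0. With c = 0.5 and r = 0.3, planned power is 77% for the 40-school plan; for the recruited sample it is 84% against 94%.

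**5. The optional baseline covariate.** With both visits present, each child contributes a change and a sum. Under random intercepts, only the changes inform the interaction. A covariate that takes the same value at both visits, entered as a main effect, drops out of the change, so the interaction estimate does not move. In three simulated complete datasets (participant-intercept model) the estimate was identical to numerical precision, while the reported standard error fell by about 7-8%. The reported error shrank, but the estimator did not improve.

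**The case against.** The strongest reply is that nothing here is wrong: a mixed-model difference in change is standard, unbiased under randomization, and matches the Abstract's endpoint. That stands.

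A reader might infer that the plan throws away 15-35% of its precision, or that the trial is underpowered. The documents support neither as a general statement. The range rests on an assumed R of 0.3-0.7; under the plan's own covariance structure the loss is smaller and no shortfall occurs. A shortfall needs school effects that drift over five years, and over-recruitment to 50 schools lowers the threshold to about 0.37. In the other direction, c = 1 is a modelling choice in the plan and not evidence that schools are stable.

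It can also be said that baseline adjustment is not confined to sensitivity analysis, because the plan allows it in the main models. The wording does allow it, but it is optional, and step 5 shows that it would not deliver ANCOVA's gain.

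Finally, the efficiency comparison presumes comparable arms. Children enrolled by individual consent, 588 in 26 schools against 389 in 24 (22.6 against 16.2 per school), and the article does not say whether consent preceded allocation. This stands as a caution, chiefly against forcing equal baseline means.

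**Conclusion.** The point holds as a conditional efficiency gain. The planned primary estimator is an unconstrained difference in change, and ANCOVA would have (1+R)/2 of its variance. The reduction is 15-35% for R of 0.3-0.7, or about 11-22% if school effects are constant and the child correlation is 0-0.5. Power below the stated 80% requires R under about 0.48 (40 schools) or 0.37 (as recruited, no loss), and hence drifting school effects. These sizes rest on equal SDs at both times, the plan's ICC and cluster-size variation, and an R that the documents do not supply. Neither bias nor invalid inference in the planned interaction estimate is shown.

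**What to change.** Before 5-year data are available (the study timeline runs to 2031):

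- Make the primary analysis a regression of the 5-year score on arm, the child's baseline score, the school-mean baseline score and school type, with a random school intercept.
- Move the unconstrained time-by-group interaction to the sensitivity analyses.
- Delete the optional baseline-outcome covariate from the repeated-measures model.

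The cost is a change of analysis-plan wording; ANCOVA and baseline adjustment are already named there. Children without a baseline score would need imputation, whereas the present likelihood model uses them directly. A baseline-constrained longitudinal model with school-by-time random effects would avoid that, but it is an alternative only if recruitment was not differential by arm, which the 588 against 389 split makes worth establishing first.

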## Methods

### Study design, population, and randomization process

The SI! Program Reintervention for Elementary Schools is a cluster-randomized trial, with schools serving as the units of randomization. In Spain, elementary education spans 6 grades and typically includes children aged 6 to 11 years. Eligible schools included public schools and charter schools initially limited to the Central, South, and East administrative areas defined by the Department of Education of the regional government of Madrid (Community of Madrid), as well as the city of Mataró (Barcelona province, Catalonia). To be eligible, schools also had to include at least one first grade class and have an operational canteen.

All schools meeting the inclusion criteria in the study areas were invited to attend informational meetings. Participation was voluntary at the school level and largely determined by institutional decisions and logistical constraints. Of the 1,026 schools in Madrid and 32 in Mataró that were invited, 50 agreed to participate. One additional school from the West administrative area of Madrid, geographically close to the boundary with the Central area, volunteered to participate and was included because it met all prespecified inclusion criteria. One school subsequently withdrew, resulting in 50 schools included in the study. Participating schools were part of the regular school systems in the study areas and represented diverse socioeconomic contexts, including public and publicly funded private schools. To reach the required sample size (see Sample Size Calculation), recruitment was conducted over 2 consecutive academic years, resulting in 2 enrollment phases: phase I (2023-2024) and phase II (2024-2025). In all, 36 schools from phase I and 15 from phase II agreed to participate (44 from Madrid and 7 from Mataró). Using block randomization stratified by school type (public vs charter), schools were assigned in a 1:1 ratio to either the reintervention group or the single-intervention group. Schools in the reintervention group were allocated to receive the SI! Program from second to sixth grade, with classroom interventions in both second and fifth grades, whereas those in the single-intervention group were allocated to receive the intervention from fifth to sixth grade, with a single classroom intervention in fifth grade (Figure 1). Schools were randomized consecutively in blocks of 6 by an independent researcher, and group allocations were communicated by email.

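### The primary mixed model has no school-by-time random effect, so its time-by-group test makes no allowance for school-level variation in 5-year change, and type I error exceeds 5% whenever that variation is present

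*Protocol article*

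**What the plan says.** Under *Study design, population, and randomization process* the trial "is a cluster-randomized trial, with schools serving as the units of randomization".

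Under *Statistical analysis plan* the primary analysis is fixed in some detail:
- Two time points: "Primary endpoint differences will be evaluated using all available measurements at baseline and at 5-year follow-up".
- Effect parameter: "The treatment effect will be estimated from the time-by-randomization interaction term, representing the between-group difference in change in SI!-Child score over time".
- Random effects: "Random intercepts for school and participant will be included to account for clustering at the school level and repeated measurements within individuals".

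The primary model is given no random school coefficient for time, no cluster-robust variance and no small-sample correction. Secondary endpoints follow the same strategy, with logistic versions for categorical outcomes. Cluster-level analyses and ANCOVA of the follow-up score appear in the same section, but only in the list of sensitivity analyses.

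Under *Sample size calculation* clustering is allowed for with "an intraclass correlation coefficient of 0.05", 20 children per school and a CV of school sizes of 0.51, "with 80% power and a 2-sided significance level of 0.05".

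**The concern.** The article says the school intercept deals with clustering by school. That is true for a comparison of score levels at one time. It is not true for the contrast the trial will test. A school intercept shifts baseline and 5-year scores by the same amount, and so does a child intercept, so both vanish when the change is formed. What remains is the within-child residual, which the model treats as independent across all children, including those in the same school.

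The model therefore assumes that, group apart, every school's mean moves identically over 5 years. The article's own description makes this doubtful. Under *School and family environment* each school's Leading group assesses its own school and chooses its own changes. The Discussion presents adaptation to local context as a strength. Under *Teacher training and implementation monitoring* differences in fidelity, dose and reach are to be measured. Both arms receive the program before the 5-year assessment, so differing school trajectories are to be expected in both.

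If schools do differ in change, part of the observed group difference is chance variation between 26 and 24 schools. The planned standard error leaves that part out, so p-values and confidence intervals for the primary endpoint would be too favourable. Continuous secondary endpoints analysed in the same way would share the fault.

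**Working it through.** **1. The plan's own figure.** Inputs from *Sample size calculation*: mean 70.62, SD 11.77, 5% difference (read as 0.05 × 70.62 = 3.531 points), 20 children per school, CV 0.51, ICC 0.05, 80% power, two-sided alpha 0.05.
- Children per arm without clustering: 2 × [11.77 × (1.960 + 0.842) / 3.531]² = 174.4, so 175.
- Design effect: 1 + [(0.51² + 1) × 20 − 1] × 0.05 = 1 + 24.202 × 0.05 = 2.21.
- Schools per arm: 174.4 × 2.21 / 20 = 19.27, so 20.

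This reproduces the stated 20 per arm. The trial was sized with a design effect of 2.21.

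**2. What the planned model tests.** For child *i* in school *j*, the score at time *t* is the fixed part + school intercept *u_j* + child intercept *v_ij* + residual *e_ijt*. Between the two waves *u_j* and *v_ij* cancel, so the change is the fixed change + (*e_ij2* − *e_ij1*), taken as independent across children. In five mixed models fitted to simulated data with school-by-time variance, the interaction estimate and standard error matched an ordinary regression of child change on group to four decimals (for example, estimate 0.2509 and standard error 0.7912 from both). The planned standard error thus has a design effect of 1.

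**3. What the variance would be.** Let CAC (cluster autocorrelation) be the correlation between a school's effects at the two waves, and *r* the correlation between a child's two scores within school. Neither is in the article, so both are assumptions.
- ICC of change = ICC(1 − CAC) / [ICC(1 − CAC) + (1 − ICC)(1 − r)].
- Design effect of change: DE = 1 + [(1 + CV²)m − 1] × ICC of change.
- Actual type I error = 2 × [1 − Φ(1.96 / √DE)].

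With m = 963 / 50 = 19.26, (1 + 0.51²) × 19.26 − 1 = 23.27. With r = 0.4, (1 − 0.05)(1 − 0.4) = 0.57.

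| CAC (assumed) | ICC of change | DE | True SE / planned SE | Type I error |
|---|---|---|---|---|
| 1.0 | 0 | 1.00 | 1.00 | 5.0% |
| 0.9 | 0.005 / 0.575 = 0.0087 | 1.20 | 1.10 | 7.4% |
| 0.8 | 0.010 / 0.580 = 0.0172 | 1.40 | 1.18 | 9.8% |
| 0.5 | 0.025 / 0.595 = 0.0420 | 1.98 | 1.41 | 16% |

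At CAC 0.8, varying *r* from 0.2 to 0.6 gives 8.6% to 12.1%.

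**4. Check by simulation.** With the realized 26 and 24 schools, an assumed 85% retention, *r* from 0.3 to 0.7 and 4,000 replicates per scenario, the planned test rejected a true null at these rates:
- CAC 1: 4.9% to 5.3%.
- CAC 0.9: 6.9% to 9.5%.
- CAC 0.8: 7.3% to 12.6%.
- CAC 0.5: 12.7% to 21.9%.

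A t test on school mean changes, which does allow for school-level change, stayed between 4.2% and 5.7% in the same scenarios.

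**The case against.** The strongest objection is that a reader might infer that the type I error simply is well above 5%. The article does not support that. It gives no ICC of change, no cluster autocorrelation and no within-child correlation, and its ICC of 0.05 is used for the score in the sample size, so it need not be the ICC of change. This is also a closed cohort: the same children are followed even if they change schools, and the introduction says parents largely determine diet and activity opportunities in early childhood. School differences that reflect stable family composition would persist and push the CAC towards 1. If school-by-time variance is negligible, the planned test is sound. This objection stands against any unconditional figure. It also rules out leaning on a CAC of 0, which gives about 25% but is an extreme case. It does not remove the fault, because the model builds in zero variance where it should estimate it.

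A second tempting inference is that the choice in "Models will be estimated using maximum likelihood", with only 50 schools, shrinks the standard error further. For the planned test it does not. That test behaves like one on up to 963 individual changes, and ML versus REML is then a factor of about √(961/963) = 0.999. The small-sample issue arises only once the model is repaired.

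Third, the cancellation is exact only for complete two-wave data in a linear model. The 963 children are those assessed at baseline, fewer will have 5-year scores, and the identity has not been shown for the logistic models. This limits the precision of the figures and any claim that every endpoint is affected to the same degree.

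Finally, the article already lists cluster-level and ANCOVA analyses. A cluster-level analysis would help to expose a result that rests on school drift. As a sensitivity analysis it leaves the primary p-value as it is.

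**Conclusion.** The point holds in conditional form. The article fixes a random-effects structure and credits it with handling school clustering, and for the time-by-group interaction it does not do so. The direction is certain: any positive school-by-time variance makes the standard error too small. The size is not known. At an assumed within-child correlation of 0.4 and the article's ICC, CV and realized school size, type I error is about 7% to 16% for an assumed cluster autocorrelation of 0.9 to 0.5. Nominal 95% intervals would then cover about 93% to 84% of the time. An ICC of change of about 0.01 is enough for roughly 7% to 8%. Because the primary test of a cluster-randomized trial depends on this, and the remedy is cheap, the plan should be changed before 5-year data are analysed.

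**What to change.** Add a random school-by-time effect (a random school coefficient for time) to the primary model and to the continuous secondary models built the same way. Fit by REML with Kenward-Roger or Satterthwaite degrees of freedom. This small-sample correction belongs to the repaired model, where the interaction is judged against variation among 50 schools. Add the corresponding school-by-time term to the logistic models.

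An alternative, though not an equivalent one, is to promote the ANCOVA of the 5-year score already listed, stated explicitly with a school random intercept and a small-sample correction. It conditions on baseline and drops children missing either wave unless they are imputed, whereas the planned model uses all available measurements.

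The cost is a short change of analysis wording, wider confidence intervals where school-level change varies, and occasional convergence problems. A simpler, uncorrelated random-effects structure can be prespecified as the fallback for those. The study timeline runs to 2031, so there is time to make the change.
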